### Objective two: development of a theory-based hospital-level knowledge translation intervention to increase the number of DCD organ donors in Canada that is based on the identified determinants

Using the data obtained in objective one, we will develop a theory-based knowledge translation intervention that encompasses behavior change techniques to overcome the identified barriers and enhance the enablers to DCD. We will use the principles of intervention mapping, a formal systematic process for building interventions based upon determinants to behaviour change [36], to design the intervention. A three step procedure will be followed. First, the team will meet to prioritize the relevant TDF domains. The ‘relevant’ domains (from the analysis in objective one) will be presented to the team. After group discussion, team members will be asked to prioritize the domains on a nine-point scale [37,38]*.* We will regard domains with an overall rating of seven to nine (without disagreement) as ‘high priority’ for our intervention [38]. Second, the knowledge translation researchers on the team ([name], [name]) along with the study research assistant (SL) will map behaviour change techniques onto the belief statements in the ‘high priority’ domains from step one above using the Michie Behavior Change Matrix [39], which comprises a list of 53 effective behaviour change techniques. Third, a meeting of the research team along with provincial organ donor coordinators and intensivists will occur to finalize the content of the KT intervention and determine possible modes of delivery of the intervention. The intervention techniques chosen and delivery will be based on: empirical evidence and expert consensus of the effectiveness of the behavior change techniques; what is likely to be feasible in our context; and what is locally relevant and acceptable. There are many potential delivery modes in the clinical setting for most behavior change techniques, including facilitated workshops, educational meetings, educational outreach (or academic detailing), local opinion leaders, reminder systems, and audit and feedback [40]. As an example, we might use a facilitated workshop led by a respected clinician with extensive DCD experience. Follow-up from the workshop may include personal auditing and feedback of performance with respect to DCD. These are just examples; the content and delivery of the intervention will be determined jointly by the research team and provincial organ donor coordinators, and in consideration of the barriers and enablers data and the mapping process to be undertaken.

### Objective three: national implementation and evaluation for effectiveness of the knowledge translation intervention using a multiple interrupted time-series design

The final phase of our study involves rolling out the knowledge translation intervention developed for objective two in hospitals across the 10 Canadian provinces and evaluating it using a multiple interrupted time series (ITS) design. ITS is a powerful design to evaluate the effect of an experimental intervention or policy change that is introduced at a specific point in time, when repeated measures of an outcome of interest are available before and after the introduction of the intervention, and when randomization is not feasible. Segmented regression analysis is used to control for secular trends by estimating changes in intercepts and slopes from before to after the introduction of the intervention. Both an immediate impact (change in intercept) and gradual changes over time (change in slope) can be detected [41]. This design is immune against common threats to internal validity of observational study designs, including maturation and regression to the mean.

### Outcome measures

The primary outcome measure for evaluation of the knowledge translation intervention will be total donation rate (defined as the total number of organ donors, NDD plus DCD combined) per million population (PMP) per six months. Although a change in the DCD rate might seem to be a more appropriate outcome measure, we chose the total donation rate for two reasons. First, there is a concern that increased use of DCD might lead to fewer NDD donors [42]. If our intervention was successful at increasing DCD donors but led to a reduction in NDD donors, this would not be considered a positive intervention that should be adopted. If this occurred, use of the DCD rate alone as the primary outcome could potentially mislead stakeholders that our intervention should be implemented. By using the total donation rate, we will judge our intervention to be successful only if total donors increase. We hypothesize that there will be an increase in the total donation rate that is driven by an increase in the DCD rate with a neutral or even positive effect on the NDD donor rate as has been recently seen in the province of Ontario [43]. Second, since routine use of DCD only resumed in 2006 in Canada, observed DCD counts were all zero until 2005 and too small thereafter (<5 per million) to allow stable analysis of six-month intervals as planned (only seven pre- and three post-intervention time points for analysis). In contrast, the number of time points available for NDD and total donations is at least 30 (24 pre-, six post-intervention). So from a statistical perspective as well, total donation rate is the preferred primary outcome. Secondary outcome measures will be DCD rate (PPM per year) and (NDD) rate (PPM per six months).

### Analysis plan

The proposed method of analysis is a segmented linear regression autoregressive error model of the observed aggregate outcomes in each of four regions that comprise the 10 Canadian provinces: Atlantic Canada (New Brunswick, Nova Scotia, Prince Edward Island, and Newfoundland), Ontario, Quebec, and Western Canada (British Columbia, Alberta, Saskatchewan, and Manitoba). This approach is commonly used in health services research because it can tolerate fewer time points than autoregressive integrated moving average (ARIMA) models and is amenable to intuitive graphical presentation [41]. The first step of the analysis will be a graphical inspection of donation rates over time, at six-month intervals, in each of the study regions. The full model will be fitted by specifying a pre-intervention intercept and slope, and two parameters that represent the change in intercept and change in slope after introduction of the intervention. Maximum likelihood estimation will be used as it is considered one of the most appropriate methods of estimation for small samples with autocorrelated errors [44]. The analysis will adjust both parameter and variance estimates for autocorrelation. No adjustment for seasonal trends is anticipated.

The significance of the knowledge translation intervention will be evaluated using a likelihood ratio test of the change parameters. The null hypothesis is that both intercept and slope changes are zero; the alternative hypothesis is that at least one of intercept or slope change is non-zero. The immediate and gradual effect of the knowledge translation intervention will be estimated using confidence intervals for both absolute and relative change in the intercept and slope, using methods developed by Zhang *et al.*[45]. The overall effect, combining intercept and trend changes, will be estimated using the absolute and relative difference in the predicted post-intervention outcome versus the predicted outcome from the secular trend (counterfactual estimate) together with confidence intervals, using the methods developed by Zhang *et al.*[45]. As recommended, we will report 95% confidence intervals using the 99% critical value to account for the fact that time series with a small number of time points and large autocorrelation may produce artificially narrow confidence intervals.

To assess the fit of the final model, we will examine residual plots around the predicted regression lines. The residual plots will be used to check whether the linear assumption for the segmented regression model is satisfied. If the linear assumption is not satisfied, either log-transformation of the outcome or Poisson regression with population size as an offset term will be carried out.

Due to the limitations of our sample size (a minimum of 30 time points) we will conduct sensitivity analyses using methods recently developed for short interrupted time series. First, we will use the double-bootstrap approach developed by McKnight *et al.*[46] who demonstrated that empirical coverage and type I error rates are close to the nominal levels for as few as 20 observation times. Second, we will use the restricted maximum likelihood (REML) approach together with Kenward-Roger degrees of freedom investigated by Forbes *et al.*[47]. They showed that type I error rates of this approach are close to nominal size with as few as 30 observation times. Finally, for the secondary analysis of DCD rates, we anticipate only three available post-intervention observation points (at annual intervals) which is insufficient to reliably estimate a parametric trend after the intervention. Following Bloom [48], we will specify post-intervention time for DCD as a categorical variable (*i.e.*, post-intervention change will be estimated as deviations from the pre-intervention trend in post-intervention years one, two, and three).

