## Methods

### Design and objectives

This is a five-year multi-phased study that will use state of the art approaches from knowledge translation science and health psychology to systematically develop a theory-based knowledge translation intervention to change institutional, team, and clinician behavior in order to increase the number of DCD donors in Canada. This population-level evaluation study will use a multiple interrupted time series design to assess the effectiveness of the intervention in the 10 Canadian provinces: British Columbia, Alberta, Saskatchewan, Manitoba, Ontario, Quebec, New Brunswick, Nova Scotia, Prince Edward Island, and Newfoundland.

Our specific objectives are to:

1. Understand the process of, and identify the determinants to, DCD as perceived by healthcare professionals (organ donor coordinators, intensive care nurses, intensive care physicians (intensivists)) across Canada *(*Medical Research Council Complex Interventions Framework- Phase zero, Knowledge-to-Action- assessing determinants of knowledge translation*)*

2. Develop a theory-based hospital-level knowledge translation intervention to increase the number of DCD organ donors in Canada that is based on the identified determinants (Medical Research Council Complex Interventions Framework—Phases one and two, Knowledge-to-Action - selecting, tailoring knowledge translation interventions)

3. Conduct a national implementation and evaluation for effectiveness of the knowledge translation intervention using a multiple interrupted time-series design (Medical Research Council Complex Interventions Framework—Phase three, Knowledge-to-Action—implementing and evaluating knowledge translation interventions)

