### Power calculations

Power calculations were carried out using the simulation approach developed by Zhang *et al.*[49]. The assumptions for the power calculations were as follows: mean square error (MSE), baseline intercept, and trend equal to the observed pre-intervention values in each region; change in intercept = 0; alpha = 5%; 24 data points before and six after the intervention (N = 30 data points in total). Zhang and colleagues [49] recommend a plausible range of r = 0.1 to r = 0.5 for the autocorrelation parameter [AR(1)]. To assess sensitivity with respect to the strength of autocorrelation, we conducted the power calculations for r = 0.4 as well as very strong correlation of r = 0.8 (Table 3). A summary of the required effect sizes **Δ** (change in slope) to yield 80% power for the likelihood ratio test of the intercept and slope changes in each region are presented in Table 3 as both absolute and relative changes. With at least 30 time points and assuming moderate autocorrelation, we will have 80% power (α = 0.05) to detect annual% changes in total donations of 8.5% in the West, 5.6% in Quebec, 7.8% in Ontario, and 14.0% in the Atlantic Provinces.

**Table 3 T3:** **Power calculation**^
**1 **
^**for ITS study**

	**Δ**^ **3** ^**donation rate (per million population per six months)**		**Δ donation count (per year based on 2011 population size)**^ **3** ^		**%Δ donation count (per year relative to 2011)**^ **3** ^	
AR(1)^2^	r = 0.4	r = 0.8	r = 0.4	r = 0.8	r = 0.4	r = 0.8
West	0.47	0.70	10.0	14.9	8.5%	12.6%
Quebec	0.48	0.73	7.7	11.7	5.6%	8.5%
Ontario	0.64	0.95	17.1	25.4	7.8%	11.5%
Atlantic	1.25	1.87	5.9	8.8	14.0%	21.0%

^1^The assumptions for the power calculations were as follows: (a) mean square error (MSE), baseline intercept, and trend equal to the observed pre-intervention values in each region; (b) change in intercept = 0, (c) alpha = 5%; (d) 24 data points before and six after the intervention (N = 30 data points in total).

^2^AR(1) = autocorrelation parameter.

^3^Δ = required effect sizes (change in slope).

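### Objective three asks a national question, but the article fits, tests and powers four separate regions at 5% each, and describes no national test, decision rule or multiplicity control

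*Protocol article*

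**What the plan says.** The third objective (Design and objectives) is to "Conduct a national implementation and evaluation for effectiveness of the knowledge translation intervention using a multiple interrupted time-series design". The heading of the objective three section repeats that national scope.

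The Analysis plan then works by region. It specifies one "segmented linear regression autoregressive error model of the observed aggregate outcomes in each of four regions that comprise the 10 Canadian provinces". Those regions are Ontario, Quebec, Western Canada and Atlantic Canada. On inference it says that "The significance of the knowledge translation intervention will be evaluated using a likelihood ratio test of the change parameters", and that "the alternative hypothesis is that at least one of intercept or slope change is non-zero".

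The Power calculations section confirms that this test is applied region by region. The assumptions are "alpha = 5%; 24 data points before and six after the intervention (N = 30 data points in total"), and the effect sizes in Table 3 are those giving "80% power for the likelihood ratio test of the intercept and slope changes in each region". The summary is also regional: "we will have 80% power (α = 0.05) to detect annual% changes in total donations of 8.5% in the West, 5.6% in Quebec", with 7.8% for Ontario and 14.0% for the Atlantic provinces. No national figure is given.

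The Outcome measures section gives the only success criterion: the intervention succeeds only if total donors rise. It does not say whether that means nationally, in any region or in every region.

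**The concern.** The stated question has one answer, namely whether the intervention raised donation in Canada. The described analysis produces four. Two problems follow.

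- **No verdict is defined.** With four tests at 5% and no rule, a result such as one region significant and three not can be argued either way after the data are seen. The error rate of the overall conclusion is then undefined.
- **Information is not combined.** A real effect of similar modest size in all four regions may reach significance in none of them, although the national series would show it.

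**Working it through.** **Inputs.** From the Power calculations section and Table 3: alpha 5% per region; 24 points before and 6 after; detectable slope change at r = 0.4 of 0.47 (West), 0.48 (Quebec), 0.64 (Ontario) and 1.25 (Atlantic) per million per six months; yearly count changes of 10.0, 7.7, 17.1 and 5.9. The cross-region correlations below are assumptions, because the article gives none.

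**1. The plan's own figures.** The regional mean square errors are not printed, so the 80% power cannot be reproduced in absolute terms. The ratio of detectable change at r = 0.8 to that at r = 0.4 does not depend on scale and can be checked:

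- Table 3: 0.70/0.47 = 1.49, 0.73/0.48 = 1.52, 0.95/0.64 = 1.48, 1.87/1.25 = 1.50.
- Simulation of the planned test (maximum likelihood, AR(1) errors, 24 + 6 points, 2-df likelihood ratio, mean square error taken as innovation variance): 1.54, roughly consistent.

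**2. Error rate if any one region were enough.**

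- Four independent tests of exact 5% size, either direction: 1 − 0.95⁴ = 18.5%.
- Bounds under dependence: 5% (complete dependence) to 4 × 5% = 20%.
- Simulation with each test calibrated to 5% and r = 0.4: 18.5%, 18.4%, 16.7%, 10.8% and 5.1% at cross-region correlations of 0, 0.3, 0.6, 0.9 and 1.0.
- False increases only, independent tests: 1 − 0.975⁴ = 9.6%.
- If all four regions had to be significant: 0.05⁴ = 0.0006%.

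**3. What a national test could detect.** With the same design and the same r in every region, the detectable slope change is proportional to its standard error. Table 3 therefore fixes the relative standard errors, and no residual SD need be assumed.

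Population implied by Table 3 = yearly count / (2 × rate). The factor 2 cancels from the weights.

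| Region | Implied population (millions) | Weight w | Δ | w × Δ |
|---|---|---|---|---|
| West | 10.64 | 0.309 | 0.47 | 0.145 |
| Quebec | 8.02 | 0.233 | 0.48 | 0.112 |
| Ontario | 13.36 | 0.389 | 0.64 | 0.249 |
| Atlantic | 2.36 | 0.069 | 1.25 | 0.086 |
| Total | 34.38 | 1 | | 0.592 |

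National Δ = √[(1 − c) Σ(wΔ)² + c (ΣwΔ)²], where c is the cross-region error correlation, Σ(wΔ)² = 0.1029 and (ΣwΔ)² = 0.3504.

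- c = 0: √0.1029 = 0.32
- c = 0.3: √(0.0720 + 0.1051) = 0.42
- c = 0.6: √(0.0412 + 0.2102) = 0.50

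The regional values run from 0.47 to 1.25. At c = 0.6 the national value is slightly above those of West (0.47) and Quebec (0.48).

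**4. What the regional tests would do with a common change of 0.32.** The noncentrality for 80% power on 2 df at 5% is 9.63. Each region's noncentrality is 9.63 × (0.32/Δ)², which gives asymptotic power of about 46% (West), 44% (Quebec), 27% (Ontario) and 10% (Atlantic). With independent regional errors, the national test would have 80%.

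**The case against.** **The article states no any-region rule.** This stands. A reader might infer that the chance of a false success is at least 18.5%, but the document does not support that. The figure needs independent tests, exact 5% size, an any-region rule, and significant decreases counted as successes. The success criterion is an increase, dependence lowers the figure, and an all-regions rule would make it negligible. The defect is the missing rule.

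**A still higher rate might be quoted.** The planned likelihood ratio test with the chi-square cut-off is oversized in 30-point series: its simulated size was 14.1% at r = 0.4, which would give about 45% for any significant region under independence. That is a separate small-sample problem, which the article partly addresses with its double-bootstrap and REML with Kenward-Roger sensitivity analyses. It should not be charged to multiplicity.

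**The 99% critical value might seem to help.** It applies to the confidence intervals and is justified by short autocorrelated series. It does not change the regional tests.

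**The gain from combining regions is not assured.** This also stands. National shocks are plausible, and at a correlation of 0.6 the gain over the two most precise regions is gone. The argument for a single national test rests on the objective and does not need the gain.

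**Regional results matter.** They do: in 2011 donation after cardiocirculatory death ranged from 0% to 20% of deceased donors across provinces. That supports reporting regional effects, but not leaving the national question without a test.

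**A condensed article may omit a pooled analysis.** Possible, so the claim is only that none is described. But the article does fix the model, test, hypotheses and power, and all are regional.

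**Conclusion.** The point holds as a mismatch between a national objective and a regional primary analysis with no combining rule. If any significant region counted, the false-positive chance would be about 18.5% for independent tests of exact size (range 5% to 20%), and about 9.6% for a false increase. In sensitivity, a national slope change of about 0.32 would be detectable at r = 0.4 against 0.47 to 1.25 by region. This assumes independent regional errors, a common r and weights implied by Table 3. It becomes 0.42 and 0.50 at assumed correlations of 0.3 and 0.6. The mismatch itself depends on none of these assumptions. It should be corrected before the post-intervention data are analysed.

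**What to change.** - Name one primary estimand: the population-weighted national difference between the predicted post-intervention rate and its counterfactual. One direct route is to fit the same segmented model to total donors over total population of the 10 provinces. That series carries any cross-region correlation, so none has to be assumed in the analysis.
- Test it once at 5%, and state that success means a significant national increase.
- Report the four regional effects and their heterogeneity as secondary. If any regional claim is to be made, use Holm-adjusted p-values (smallest p-value against 0.05/4 = 1.25%).
- Restate power for the national test from the observed national pre-intervention series, and keep Table 3 as supporting information.

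**Cost.** Analysis-plan wording, one further model fit and a new power run, with no new data. The downside is that the national figure averages over real regional differences, though these are still reported.

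### The primary likelihood ratio test does not hold its 5% level on a 30-point series, and the stated 80% power appears to rest on that uncorrected test

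*Protocol article*

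**What the plan says.** All references are to the protocol article, Objective three.

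- **Estimation** (Analysis plan): a segmented linear model with autoregressive errors in each of four regions. "Maximum likelihood estimation will be used as it is considered one of the most appropriate methods of estimation for small samples with autocorrelated errors".
- **Primary test** (Analysis plan): "The significance of the knowledge translation intervention will be evaluated using a likelihood ratio test of the change parameters". It is a joint, non-directional test: no change in level or trend, against a change in either or both. No reference distribution or small-sample correction is given for the test.
- **Intervals** (Analysis plan): because short, autocorrelated series can give intervals that are too narrow, "we will report 95% confidence intervals using the 99% critical value".
- **Sensitivity analyses** (Analysis plan): a double bootstrap, described as near nominal from 20 observation times, and REML with Kenward-Roger degrees of freedom, of which the article says: "They showed that type I error rates of this approach are close to nominal size with as few as 30 observation times".
- **Power calculations**: 80% power for the likelihood ratio test at alpha 5%, zero intercept change, "24 data points before and six after the intervention (N = 30 data points in total"). Autocorrelation is set to 0.4 and 0.8, and 0.1 to 0.5 is cited as plausible.

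**The concern.** The article recognises that a short autocorrelated series defeats large-sample inference. It acts on this for the intervals and in the sensitivity analyses, but not for the test that decides significance. With four regression coefficients and 30 points, maximum likelihood underestimates the autocorrelation, so the likelihood ratio statistic is too large under the null hypothesis.

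Two things are at stake. The p-value in each region would be smaller than the evidence warrants, and the power statement would describe a test whose real level is well above 5%. Test and intervals can also disagree, because the test uses the ordinary cutoff and the intervals a stricter one. The article does not say how to read such a result.

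**Working it through.** **Inputs.** From the article: 24 + 6 points, alpha 5%, 80% power, intercept change 0, r = 0.4 and 0.8, plausible range 0.1 to 0.5, and the Table 3 slope changes. Assumed: chi-square(2) reference, Gaussian AR(1) errors, a correct linear trend, and a slope term coded 1 to 6 after the intervention. Regional mean square errors are not given. Type I error does not depend on them.

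**Model and test.** y_t = b0 + b1·t + b2·P_t + b3·S_t + e_t, with e_t = r·e_(t−1) + u_t, where P_t marks the post-intervention period and S_t counts its half-years. LR = 2(l_full − l_null), both by exact maximum likelihood with r profiled. The 5% cutoff is −2·ln(0.05) = 5.99; the 1% cutoff is −2·ln(0.01) = 9.21.

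**Step 1: reproduce Table 3.** With cutoff 5.99, 80% power needs a slope change of 0.642 innovation SDs at r = 0.4 and 0.966 at r = 0.8. One SD per region is solved from the r = 0.4 column, and the r = 0.8 column is then predicted.

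| Region | r = 0.4 | Implied SD | Predicted r = 0.8 | Stated r = 0.8 | Stated ratio |
|---|---|---|---|---|---|
| West | 0.47 | 0.47/0.642 = 0.73 | 0.71 | 0.70 | 1.49 |
| Quebec | 0.48 | 0.75 | 0.72 | 0.73 | 1.52 |
| Ontario | 0.64 | 1.00 | 0.96 | 0.95 | 1.48 |
| Atlantic | 1.25 | 1.95 | 1.88 | 1.87 | 1.50 |

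Power at the stated r = 0.8 effects is 79.5%, 80.7%, 79.2% and 79.8%. The uncorrected test implies a ratio of 0.966/0.642 = 1.50; a size-corrected test implies 1.64. Table 3 therefore fits the uncorrected test.

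**Step 2: size and power.** Results over repeated runs of 8,000 to 40,000 series (at 40,000 runs the standard error for r = 0.4 is √(0.139 × 0.861/40,000) = 0.2 points). The power column is power at a true 5% level, for the effect at which the nominal test shows 80%.

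| r | Type I error, cutoff 5.99 | Cutoff for a true 5% | Power at a true 5% |
|---|---|---|---|
| 0 | 10.6–11.0% | 7.9–8.1 | 65–66% |
| 0.1 | 11.3–11.7% | 8.1–8.2 | 64–65% |
| 0.4 | 13.7–14.1% | 8.9–9.1 | 57–60% |
| 0.5 | 14.4–15.1% | 9.3–9.5 | 55–57% |
| 0.8 | 18.8–19.4% | 10.6–10.8 | 50–54% |

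At a true r of 0.4 the mean maximum likelihood estimate is about 0.20, which is the mechanism described above.

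**Step 3: effects for a true 80% at r = 0.4.** The required slope change rises by a factor of 1.27 to 1.29. At 1.29: West 8.5% × 1.29 = 11.0%, Quebec 5.6% × 1.29 = 7.2%, Ontario 7.8% × 1.29 = 10.1%, Atlantic 14.0% × 1.29 = 18.1%.

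**Step 4: the plan's 99% rule applied to the test.** With cutoff 9.21 the size is 3.3–3.6% at r = 0.1, 4.6–4.8% at 0.4, 4.7–5.4% at 0.5 and 7.6–7.8% at 0.8.

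**Step 5: test against intervals.** Under the null at r = 0.4, 10.6 of 14.0 percentage points of rejections had at least one interval (level, slope or end-of-follow-up effect, multiplier 2.576) excluding zero. The other 3.4 points, about a quarter of rejections, were significant with all three covering zero.

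**The case against.** Four points on the other side deserve weight.

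- **The reference distribution is not stated.** Chi-square(2) is the default reading, and a full analysis plan might name another. The match with Table 3 supports the default for the power calculation, but it rests on back-solved SDs and the slope coding. With coding 0 to 5 the uncorrected ratio is 1.44, a looser fit. This is an inference, not proof.
- **Thirty points is a minimum.** With 6 or 12 more pre-intervention points, type I error at r = 0.4 falls to about 10–12%. That is smaller, but still at least twice nominal.
- **The problem is acknowledged.** Two small-sample analyses are prespecified, so a reader would see a discordant result. It is therefore too strong to say that the article ignores the issue. But no rule says which result prevails, and the primary test and stated power stay uncorrected.
- **The rejection rate is not a false-success rate.** A reader might infer that an ineffective intervention would be declared effective 14% of the time. The article does not support that: the test is non-directional, and under Outcome measures only an increase in total donors counts as success. By symmetry about 14/2 = 7% of null series reject with a positive estimate on any one measure of effect; one direct count gave 5.8%. Against a nominal 2.5% that is a factor of 2.3 to 2.8, similar to 14/5 = 2.8 for the two-directional test.

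A reader might also infer that a bootstrap of the likelihood ratio statistic is already planned, or that the 99% rule must go. The article does not say what its double bootstrap resamples, and Step 4 shows that the 99% rule, extended to the test, nearly restores the level within the plausible range.

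**Conclusion.** The point holds, conditional on r. With 24 + 6 points, AR(1) errors and a chi-square(2) reference, the primary test's two-directional type I error is about 11–15% for r = 0.1 to 0.5 and about 19% at 0.8. It exceeds 5% even at r = 0, so no value in the plausible range rescues it.

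The stated 80% power at alpha 0.05 corresponds to about 55–65% at a true 5% level for r = 0.1 to 0.5 and to about half at 0.8. The figures of 14% and 59% belong to r = 0.4 with exactly 30 points and should not be quoted without those conditions. The size results need no regional variance. The reading of Table 3 does rest on back-solved values, so it confirms how the two columns relate but not the absolute effect sizes.

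**What to change.** 1. Take the primary p-value from a size-controlled procedure. Either promote one of the small-sample methods now listed as sensitivity analyses (REML with Kenward-Roger, or the double bootstrap), or keep the likelihood ratio test and apply the plan's own 99% critical value, 9.21, to it.
2. Before fixing the choice, check its size by simulation at 24 + 6 points for the joint two-parameter hypothesis over r = 0.1 to 0.8. None of the options should be assumed exact: the 9.21 cutoff still gives nearly 8% at r = 0.8, and a trial parametric bootstrap of the likelihood ratio statistic gave 8.7% there in only 300 runs.
3. Report intervals consistent with the chosen test, and keep the 5.99 test as a sensitivity analysis only.
4. Restate Table 3 and the closing sentence of Power calculations for that test, as lower power at the listed effects or as larger detectable effects.

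The cost is a change of wording and a rerun of the power simulation, with no new data. The price is a less favourable power statement.
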